#### 4.6. Time and Events Table

Detailed procedure and time window please reference to SPM

**Table 2 Study Procedures**

| Procedure                                   | Screening      | day in each period |       |       |       |       |       |       |       |       |       |        |                |                | Follow-Up                 |
|---------------------------------------------|----------------|--------------------|-------|-------|-------|-------|-------|-------|-------|-------|-------|--------|----------------|----------------|---------------------------|
|                                             |                | Day - 1            | Day 1 | Day 2 | Day 3 | Day 4 | Day 5 | Day 6 | Day 7 | Day 8 | Day 9 | Day 10 | Day 11         | Day 12         | 7-10 days after last dose |
| Admission to the unit                       |                | X      |       |       |       |       |       |       |       |       |       |        |                |                |                           |
| Discharge from the unit                     |                |                    |       |       |       |       |       |       |       |       |       |        |                | X  |                           |
| Training session                            |                | X                  |       |       |       |       |       |       |       |       |       |        |                |                |                           |
| Informed consent                            | X              |                    |       |       |       |       |       |       |       |       |       |        |                |                |                           |
| Medical history, height & weight            | X              |                    |       |       |       |       |       |       |       |       |       |        |                |                |                           |
| Chest Radiography                           |                | X      |       |       |       |       |       |       |       |       |       |        |                |                |                           |
| Physical examination,                       | X  |                    |       |       |       |       |       |       |       |       |       |        |                |                | X             |
| Serology (HIV, Hep B & C)                   | X              |                    |       |       |       |       |       |       |       |       |       |        |                |                |                           |
| Drugs of abuse screen                       | X              |                    |       |       |       |       |       |       |       |       |       |        |                |                |                           |
| Alcohol breath test and urine cotinine test | X              | X                  |       |       |       |       |       |       |       |       |       |        |                |                |                           |
| Laboratory safety tests         | X              | X      |       |       |       |       |       |       |       |       |       |        | X              |                | X             |
| Vital signs (HR and BP)                     | X  | X                  | X     | X     | X     | X     | X     | X     | X     | X     | X     | X      | X              | X              | X                         |
| 12-lead ECG                                 | X  |                    | X     |       |       |       |       |       |       |       |       | X      | X              | X              | X                         |
| Urine pregnancy test                        | X              | X      |       |       |       |       |       |       |       |       |       |        | X  |                |                           |
| Review entry criteria                       | X              | X                  |       |       |       |       |       |       |       |       |       |        |                |                |                           |
| Randomization                               |                | X     |       |       |       |       |       |       |       |       |       |        |                |                |                           |
| Dosing (AM)                                 |                |                    | X     | X     | X     | X     | X     | X     | X     | X     | X     | X      |                |                |                           |

| Procedure                                              | Screening | day in each period |       |       |       |       |       |                 |                 |                 |                 |        |        |        | Follow-Up |
|--------------------------------------------------------|-----------|--------------------|-------|-------|-------|-------|-------|-----------------|-----------------|-----------------|-----------------|--------|--------|--------|-----------|
|                                                        |           | Day -1             | Day 1 | Day 2 | Day 3 | Day 4 | Day 5 | Day 6           | Day 7           | Day 8           | Day 9           | Day 10 | Day 11 | Day 12 |           |
| Blood PK sampling                                      |           |                    | X     |       |       |       |       | X  | X  | X  | X  | X      | X      | X      |           |
| Unit visit                                             | X         |                    |       |       |       |       |       |                 |                 |                 |                 |        |        |        | X         |
| SAE/AE/concurrent medication questioning  | X         |                    |       |       |       |       |       |                 |                 |                 |                 |        |        |        |           |

1. On day -1 subjects will attend the unit and will be resident until all assessments completed on day12.
2. If a chest X-ray or CT scan is not available within 6 months prior to screening.
3. Physical examination means complete one.
4. Brief physical examination only.
5. Clinical chemistry, haematology & urinalysis.
6. These assessments are taken Day -1 in treatment period 2 and 3.
7. Abnormal lab safety findings post-dosing should be followed up until the tests are normal, stable, no causal relationship with investigational product judged by investigators, or lost contact.
8. Three measurements are to be taken.
9. The test will be taken on Day 11 in the last treatment period.
10. Only on Day-1 in the first treatment period.
11. Blood PK sample will be collected only pre-dosing.
12. AEs and SAEs will be collected from the start of dosing with Investigational Product and until the follow-up visit. However, any SAEs related to study participation or a GSK concomitant medication will be recorded from the time a subject consents to participate in the study and until the follow-up visit.

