### 4. INVESTIGATIONAL PLAN

#### 4.1. Study Design/Schematic

This is a single centre, randomized, open label, 3-period crossover, balanced incomplete block study in healthy Chinese subjects.

All subjects will attend the unit for screening within 21 days of their first of three dosing periods. Each subject will receive three of the five treatment regimens described in [Table 1](#) below.

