
### **5.2.2. Exclusion Criteria**

Deviations from exclusion criteria are not allowed because they can potentially jeopardize the scientific integrity of the study, regulatory acceptability or subject safety. Therefore, adherence to the criteria as specified in the protocol is essential.

A subject will not be eligible for inclusion in this study if any of the following criteria apply:

1. As a result of medical interview, physical examination or screening investigations, the principle investigator or delegate physician deems the subject unsuitable for the study.
2. History of mental, cardiac, renal, hepatic, significant gastrointestinal or respiratory disease as judged by the investigator
3. A history of breathing problems (i.e. history of asthmatic symptomatology, unless asthma in childhood that has now resolved and no longer requires maintenance therapy which should not be an exclusion).
4. A chest X-ray or computed tomography (CT) scan that reveals evidence of clinically significant abnormalities. A chest X-ray must be taken at day -1 of the first treatment if a chest X-ray or CT scan is not available within 6 months prior to that day.
5. History of sensitivity to heparin, heparin-induced thrombocytopenia, or sensitivity to any of the study medications, or components thereof, known allergy or hypersensitivity to milk protein or the excipients lactose monohydrate and magnesium stearate (MgSt), or a history of drug or other allergy that, in the opinion of the investigator or GSK Medical Monitor, contraindicates their participation.
6. The subject has taken prescription or non-prescription drugs, including CYP3A/PGP inhibitor, vitamins, herbal and dietary supplements (including St John's Wort) within 7 days (or 14 days if the drug is a potential enzyme inducer) or 5 half-lives (whichever is longer) prior to the first dose of study medication, unless in the opinion of the Investigator and Sponsor the medication will not interfere with the study procedures or compromise subject safety.
7. Positive result of urine cotinine test.
8. The subject has a history of cholecystectomy or biliary tract disease.

9. The subject has a significant clinical history or current conditions of glaucoma.
10. The subject has a significant clinical history or current conditions of prostatic hypertrophy.

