11. The subject has a positive pre-study drug screen. A minimum list of drugs that were screened for included amphetamines, barbiturates, cocaine, opiates and benzodiazepines. The detection of drugs with a legitimate medical use was not necessarily an exclusion to study participation. The detection of alcohol was not an exclusion at screening but had to be negative pre-dose and during the study.
12. History of regular alcohol consumption within 3 months of the study defined as:
  - Abuse of an average weekly intake of greater than 21 units or an average daily intake of greater than three units (males), or defined as an average weekly intake of greater than 14 units or an average daily intake of greater than two units (females). One unit was equivalent to a half-pint (220 mL) of beer or one (25 mL) measure of spirits or one glass (125 mL) of wine.
13. Female subjects, who are pregnant, planned pregnancy or lactation.
14. The subject has participated in a clinical trial and has received an investigational product within the following time period prior to the first dosing day in the current study: 30 days, 5 half-lives or twice the duration of the biological effect of the investigational product (whichever is longer).
15. Blood donation or sampled as a study subject within three months preceding the first dose of study drug and blood donation during the entire study in excess of 500mL.
16. A positive pre-study Hepatitis B surface antigen or positive Hepatitis C antibody result within 3 months of screening.
17. The subject has tested positive for HIV antibodies.
18. Unwillingness or inability to follow the procedures outlined in the protocol.
19. Subject is mentally or legally incapacitated.

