**7. STUDY ASSESSMENTS AND PROCEDURES**

This section lists the parameters of each planned study assessment. The exact timing of each assessment is listed in the Time and Events Tables (Section 4.6). Detailed procedures for obtaining each assessment are provided in the Study Procedures Manual (SPM).

Whenever vital signs, 12-lead ECGs and blood draws are scheduled for the same nominal time, the assessments should occur in the following order: 12-lead ECG, vital signs, blood draws.

Prior to being enrolled in the study and any study procedures being performed, subjects must sign the informed consent.

Each subject will undergo screening procedures within 21 days of the administration of their first dose of study medication and will have a follow up visit between 7 to 10 days inclusive post their last dose. See Section 4.6. for assessments performed at the screening and follow-up visits.

The timing and number of planned study assessments including safety or pharmacokinetic assessments may be altered during the course of the study based on newly available data (e.g. to obtain data closer to the time of peak plasma concentrations) to ensure appropriate monitoring. The change in timing or addition of time points for any planned study assessments must be approved and documented by GSK, but this will not constitute a protocol amendment. The IRB/IEC will be informed of any safety issues that require alteration of the safety monitoring scheme.

No more than 350 mL of blood will be collected over the duration of the study, including any extra assessments that may be required.

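### The Day -1 urine pregnancy test is omitted in Period 1, so the first dose rests on a screening test that may be up to 21 days old

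*Protocol*

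**What the plan says.** In the Protocol, Section 4.6, Table 2, the row "Urine pregnancy test" has three marks: screening with no footnote, Day -1 with footnote 6, and Day 11 with footnote 9. Footnote 6 reads "These assessments are taken Day -1 in treatment period 2 and 3". Footnote 9 reads "The test will be taken on Day 11 in the last treatment period".

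The timing of screening is given twice. Section 4.1 says "All subjects will attend the unit for screening within 21 days of their first of three dosing periods", and Section 7 says "Each subject will undergo screening procedures within 21 days of the administration of their first dose of study medication".

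Exclusion 13 in Section 5.2.2 bars "Female subjects, who are pregnant, planned pregnancy or lactation". Table 2 has entry criteria reviewed at screening and again on Day -1, with no footnote limiting the Day -1 review to certain periods. Randomisation takes place on Day -1 of the first period (footnote 10).

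Exclusion 4 adds imaging at the same admission for subjects without a recent film or CT: "A chest X-ray must be taken at day -1 of the first treatment". Table 2 makes this conditional through footnote 2: "If a chest X-ray or CT scan is not available within 6 months prior to screening".

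Inclusion 3 (Section 5.2.1) and Section 8.1.1 require women of childbearing potential to use contraception or abstain. Permitted methods must have a failure rate below 1%, and no time unit is given.

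**The concern.** The schedule is strictest where it matters less. Before Periods 2 and 3 a woman is tested about a day before dosing. Before her first exposure to study drug, the result relied on may be three weeks old. The Day -1 review in Period 1, which confirms eligibility on the day of randomisation, has no current result behind it for Exclusion 13.

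A site that follows the tables exactly could give all 10 doses of Period 1 to a woman who conceived after screening, or too shortly before it for the screening test to show. If she had no recent film, she could also be X-rayed on Day -1. What is at stake is fetal exposure to study drug and possibly to radiation. No estimate, confidence interval or sample-size figure is affected.

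**Working it through.** **1. Is 21 days the plan's own maximum?** The only stated figure that uses the screening window is the maximum duration of about 13 weeks (Section 4.1). Inputs: screening 21 days, three dosing periods of 10 days, two washouts of up to 14 days, follow-up up to 10 days after the last dose.

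- Simple sum: 21 + 3 × 10 + 2 × 14 + 10 = 89 days; 89/7 = 12.7 weeks.
- Washout counted from the last dose to the next first dose: 21 + 3 × 9 + 2 × 14 + 10 = 86 days = 12.3 weeks.
- Washout counted from Day 12 to the next first dose: 21 + 2 × 11 + 9 + 2 × 14 + 10 = 90 days = 12.9 weeks.

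These agree with the stated figure to within rounding, so the 21-day window belongs to the design.

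**2. Does footnote 6 exclude Period 1?** It does not contain the word only. But it names two of the three periods, and it would have no purpose if the Day -1 mark applied to all three. Footnotes 9 and 10 in the same table also tie a mark to a particular period. By contrast, the Day -1 marks for the alcohol breath and urine cotinine tests, and for the review of entry criteria, carry no such footnote.

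**3. Is the gap closed elsewhere?** Table 3 (Day 1) has no pre-dose pregnancy test. Sections 5.2, 7.2, 7.3 and 8.1 add none.

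**4. Age of the latest scheduled test.**

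| Point in time | Latest scheduled test | Maximum age |
|---|---|---|
| Period 1, Day -1 X-ray (if needed) | Screening | 21 - 1 = about 20 days |
| Period 1, first dose | Screening | 21 days |
| Periods 2 and 3, first dose | Day -1 | about 1 day |

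**5. Gap from the screening test to the next one.** With screening as day 0 and the first dose on day 21, the tenth dose falls on day 21 + 9 = 30. Counting a 7 to 14 day washout from the last dose, Period 2 starts on day 37 to 44, and its Day -1 is day 36 to 43. Counted from Day 12 instead, it is day 38 to 45. Either way the gap contains all 10 doses of Period 1.

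**6. Expected number of pregnancies.** Twenty subjects at a 1:1 sex ratio give up to 10 women. Expected conceptions = women × window in years × annual failure rate. Taking 1% as the upper limit and **assuming** that it is per year:

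10 × (21/365) × 0.01 = 0.0058, or about 0.006.

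This counts every conception in the window, although a Day -1 urine test would miss the most recent. It omits conceptions just before screening that the screening test was too early to show. Doubling the window to allow for those gives 0.012, still about one in a hundred.

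**The case against.** The strongest reply is that nothing here is a contradiction. Exclusion 13 bars pregnant women, Table 2 tests for pregnancy at screening, and the protocol nowhere promises a test within a day of every first dose. Inclusion 3 requires contraception before dosing to keep the risk low at that point, and the entry review on Day -1 still takes place. Section 4.6 refers to the Study Procedures Manual, which is not at hand, for detailed procedures, and Section 7.2 allows added safety time points.

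Much of this stands. The point is a schedule that is fixed badly, not two statements that cannot both be true. Contraception is a real safeguard, but it applies in every period and the protocol still retests before Periods 2 and 3, so it does not explain leaving out Period 1. An optional extra time point does not alter the table, and Section 4.1 calls adherence to that table essential.

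A reader might infer more than the text supports:

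- **That Exclusion 13 cannot be checked in Period 1.** It can be reviewed, but without a fresh result.
- **That every woman is X-rayed without a current test.** The film is conditional, and the documents do not say how many will need it.
- **That a pregnancy found at Period 2 would damage the analysis.** Section 7.3.2 requires withdrawal, which loses two periods. Each regimen appears 20 × 3/5 = 12 times in the sequence table in Section 4.3, so two regimens would fall to 11, still above the minimum of 10, and Sections 4.3 and 5.1 provide for replacement.
- **That the laboratory tests under footnote 6 must also be repeated.** Inclusion 7 sets the liver limits at screening, so for them the footnote is consistent.

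**Conclusion.** The concern holds as a schedule weakness. Under the current text the first exposure to study drug relies on the oldest pregnancy test: up to 21 days at the first dose and about 20 days at a Day -1 X-ray, against about 1 day in Periods 2 and 3. The next test follows all 10 doses of Period 1.

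The expected number of events is very small, about 0.006 or less on the calculation above. That rests on the failure-rate limit being annual and on all of up to 10 women being of childbearing potential. Section 7.2 allows for women who are not, so the number affected may be lower. The case does not depend on frequency. It depends on a mismatch between footnote 6 and the Day -1 eligibility review, a serious possible harm, and a very low cost of removal. A correction is worth making, but the documents do not support describing this as a likely event or as a threat to the pharmacokinetic results.

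**What to change.** Reconcile footnote 6 of Table 2 with Exclusion 13 and the Day -1 review of entry criteria. Take the urine pregnancy test row out of the Period 2 and 3 restriction, so that the protocol's own Day -1 test also applies in Period 1 and its result is available for that review. The footnote can stay as it is for the laboratory safety tests.

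In the same edit, align footnote 2 with Exclusion 4. The footnote counts the 6 months for an existing film or CT back from screening, while the exclusion criterion counts back from Day -1 of the first treatment. With up to about 20 days between those points, an older film can satisfy one and fail the other.

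The cost is two footnote edits and about 10 urine strips, at an admission where urine is already collected for the cotinine test. No extra visit or blood is needed, and the analysis does not change.

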**Table 3 Detailed Time and Events Table for Day 1**

| Procedure                                |          | Day1  |       |        |        |        |    |      |    |    |    |    |     |
|------------------------------------------|----------|-------|-------|--------|--------|--------|----|------|----|----|----|----|-----|
|                                          | Pre-dose | 0 min | 5 min | 15 min | 30 min | 45 min | 1h | 1.5h | 2h | 4h | 6h | 8h | 12h |
| Dosing                                   |          | X     |       |        |        |        |    |      |    |    |    |    |     |
| Vital Signs (BP and HR)                  | X        |       | X     | X      |        | X      |    | X    |    | X  |    | X  |     |
| 12-lead ECG                              | X        |       |       | X      |        | X      |    | X    |    | X  |    | X  |     |
| Blood PK sampling                        | X        |       | X     | X      | X      |        | X  |      | X  | X  | X  | X  |     |
| SAE/AE/concurrent medication questioning | X        |       |       |        |        |        |    |      |    |    |    |    |     |

**Table 4 Detailed Time and Events Table for Day 10**

| Procedure                                |          | Day 10 |       |        |        |        |    |      |    |    |    |    |     | Day 11         | Day 12 |
|------------------------------------------|----------|--------|-------|--------|--------|--------|----|------|----|----|----|----|-----|----------------|--------|
|                                          | Pre-dose | 0 min  | 5 min | 15 min | 30 min | 45 min | 1h | 1.5h | 2h | 4h | 6h | 8h | 12h | 24h            | 48h    |
| Dosing                                   |          | X      |       |        |        |        |    |      |    |    |    |    |     |                |        |
| Vital Signs (BP and HR)                  | X        |        | X     | X      |        | X      |    | X    |    | X  |    | X  | X   | X              | X      |
| 12-lead ECG                              | X        |        |       | X      |        | X      |    | X    |    | X  |    | X  | X   | X              | X      |
| Blood PK sampling                        | X        |        | X     | X      | X      |        | X  |      | X  | X  | X  | X  | X   | X              | X      |
| Lab safety tests                         |          |        |       |        |        |        |    |      |    |    |    |    |     | X  |        |
| SAE/AE/concurrent medication questioning | X        |        |       |        |        |        |    |      |    |    |    |    |     |                |        |

1. Blood for lab tests will be taken after the blood PK sampling

